### Data management and quality assurance

Data entry will be independently done by two researchers, and then a computer software-based error detection will be carried out to check the consistency of these data. If inconsistency occurs, the original questionnaire will be referred and the error will be corrected via a re-entry.

### Ethical approval

This study will be carried out in accordance with requirements documented in the Declaration of Helsinki. Ethics approval has been obtained from the local Health Department and the research ethics boards of Tongji Medical College, China.

### Statistical methods

Descriptive statistics will be calculated and checked for balance in intervention and control groups in demographic, health and outcome measurements at baseline. Comparisons between intervention group and control group will be performed by Chi-square (categorical variables), t test (continuous variables, normal distribution) or Mann-Whitney U test (continuous variables, skewed distribution). Final analyses will be undertaken using generalized linear mixed models to investigate changes over time in the two groups in the major outcomes. These models allow for repeated measures and can be used for normally distributed, binomial, and ordinal data [22]. All statistical analyses will be performed using SPSS 12.0 statistical software package (SPSS Inc, Chicago, IL, USA).

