### Sample size

Sample size has been calculated as the following formula [18]:

, in which *p*_*1 *_indicates incidence rate in control group, *p*_*2 *_indicates incidence rate in intervention group and  indicates average of *p*_*1 *_and *p*_*2*_. Z_α/2 _is 1.96 when significance level (α) is 0.05 and Z_β _is 1.64 for power (1 - β) is 0.90.

Take constipation, a typical diet-related digestive disorder, for example. The incidence rate of constipation in our previous study is 20.95% in the control group [16]. We aim to reduce the incidence rate by 50%, which is 10.475%, the sample size N = = 309.89 ≈ 310 for each group. On the basis of the above calculation, a sample size of 800 participants (400 in the intervention group and 400 in the control group) has been determined, considering a certain attrition rate. This sample size is adequate, with statistical power >80%, for nearly all the major outcomes, including changes in nutritional status and health status.

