### Recruitment process

The flowchart of participant's recruitment process and trial design is summarized in figure 1. Pregnancy women that are willing to take part in our study will be checked by our eligibility criteria. The eligibility criteria for enrollment includes: 1) healthy pregnant women; 2) at their third trimester; 3) had at least three routine examinations at these antenatal clinics [16]. A written consent form will be assigned by each woman to confirm her willingness to participate, and then baseline data will be collected by a questionnaire survey (main components shown in Table 1) and a consequent anthropometric measurement.

**Table 1 T1:** Overview of the Questionnaires

Categories	Items
General information	Age, residence, occupation, education level, family economic situation, height, body weight, diagnosis of diseases, family history of diseases

Basic knowledge in nutrition and health	- Food guide pyramid knowledge - Nutrient-food association knowledge - Special nutritional requirement during postpartum period

Food intake	- Frequency and amount of cereals intake - Frequency and amount of vegetables intake - Frequency and amount of fruits intake - Frequency and amount of meat intake - Frequency and amount of eggs intake - Frequency and amount of milk and its products intake - Frequency and amount of soybean and its products intake - Frequency and amount of brown sugar intake - Frequency and amount of dietary oil intake - Frequency and amount of salt intake - Frequency and amount of other substance intake (alcohol, strong tea, coffee, et al.)

Health-related behaviors and Physical activities	Teeth brushing, Bathing and Hair washing Ventilation Always lie in the bed or Get up for wandering Maternal keep-fit exercises Light physical activity or Heavy physical activity Basking in the sun

**Table 2 T2:** Comparison between Traditional Practices for "Doing the Month" and Expected Diet and Lifestyle that We Advocated during the Postpartum Period

	Traditional practices for "doing the month"	Expected diet and lifestyle during the postpartum period
**Dietary Habits**	Eat plenty of food	Increase total amount of food in accordance with energy expenditure
	
	Meat-based diet components	Diverse food with both animal foods and plant-derived foods
	

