### Interventions

On the basis of our previous study in postpartum women from Hubei province of China and the latest WHO recommendation [19], we have formed a set of recommendations for women's diet and lifestyle during the postpartum period, which is the guideline for the current intervention study. A comparison between traditional practices for "doing the month" and expected diet and lifestyle that we advocated during the postpartum period are shown in Table 1. It is obvious that our guideline emphasizes the importance of increasing consumption of vegetables and fruits, which is regard as a diet taboo for postpartum women in traditional Chinese practice. In addition, it also emphasizes the importance of maintaining energy balance through reducing excessive energy from meat, eggs and brown sugar and increasing energy expenditure from appropriate physical activity, such as doing maternal keep-fit exercises.

In the past decades, social ecological models have been increasingly used to formulate intervention strategies in comprehensive consideration, because simple interventions are unlikely to work on their own and the development of effective interventions requires strategies that affect multiple settings simultaneously [20]. As shown in Figure 2, a panel of environmental factors that influence the knowledge, belief and practice of postpartum women (the core) has been identified. Microsystem, mainly referred to family members of the individual woman, is crucial immediate environmental factors that should be considered in priority. Exosystem, including surrounding people, such as peers, friends, colleagues, neighbors and care physicians, and sources of knowledge, such as book, magazines, TV show, radio and internet, does not usually directly interact, but that can still affect the individual woman. In addition, we have to consider macrosystem, including history, culture, laws, ethnics, social conditions and economic systems, to give a personalized guide to individual postpartum woman. Previous studies by us and other groups have suggested that main influence factors on the diet and lifestyle of a postpartum woman include the woman's knowledge about postpartum nutrition and health care, the woman or her husband's educational level and family income levels, and the traditional concept learned from her mother in-law (49.4%), mother (34.0%), books and magazines (16.5%), relatives (14.3), friends or colleagues (12.6%) [15,21].

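### Baseline education, family income and knowledge, which the protocol names as main influences on postpartum diet and lifestyle, enter none of the stated comparisons, giving up a modest amount of precision

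*Protocol article*

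**What the plan says.** Two kinds of analysis appear in the Statistical methods section of the protocol article.

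- **Between-group tests:** "Comparisons between intervention group and control group will be performed by Chi-square (categorical variables), t test (continuous variables, normal distribution", with the Mann-Whitney U test for skewed continuous variables. No covariates are named.
- **Final analysis:** generalized linear mixed models for change over time in the two groups, for the major outcomes. Repeated measures are allowed for. Again no covariates are named.

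The section also plans a check of baseline balance, without saying what follows from it.

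The Interventions section, drawing on the sponsor's own and other studies, says that the "main influence factors on the diet and lifestyle of a postpartum woman include" the woman's knowledge of postpartum nutrition and care, the "educational level and family income levels" of the woman or her husband and of the family, and traditional ideas learned from relatives and other sources.

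The Recruitment process section collects baseline data by questionnaire at enrolment. Table 1 lists "Age, residence, occupation, education level, family economic situation" under general information and has a separate block on nutrition and health knowledge. The three measurable factors are therefore on file for every woman who completes the baseline questionnaire.

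**The concern.** A baseline variable that predicts the outcome can be put in the model at almost no cost. Leaving it out keeps explainable variation in the error term. Here the protocol itself names the predictors and collects them, yet neither stated analysis uses them.

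The mixed model recovers part of this where an outcome has its own baseline value. Two groups of outcomes get less from it:

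- **No baseline possible.** Uterine involution, lochia duration and puerperal infection cannot be measured in the third trimester. If they are recorded once, a change-over-time model has nothing to borrow, and the raw test is the only comparison clearly described. They belong to the group that the Outcome measurements section calls the most important.
- **Weak baseline.** The Discussion says that the traditional puerperal diet and lifestyle differ greatly from what women follow before and after that period. Antenatal diet may then predict puerperal diet poorly.

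What is at stake is interval width and power for outcomes where the Sample size section claims only that power exceeds 80%.

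**Working it through.** **1. The plan's own figure.** Inputs from the Sample size section: the normal quantile "is 1.96 when significance level (α) is 0.05"; the other quantile "is 1.64 for power (1 - β) is 0.90"; "The incidence rate of constipation in our previous study is 20.95% in the control group"; "We aim to reduce the incidence rate by 50%, which is 10.475" percent. So p1 = 0.2095, p2 = 0.10475, mean 0.157125, difference 0.10475.

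N = [1.96·√(2·0.157125·0.842875) + 1.64·√(0.2095·0.7905 + 0.10475·0.89525)]² / 0.10475²
= (1.0087 + 0.8353)² / 0.010973 = 309.89

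This reproduces the stated 309.89, rounded to 310 per group. The value 1.64 belongs to 95% power; at a true 90% the same formula gives 252. That mismatch is a separate matter and makes the trial larger. It matters here only because it leaves constipation well powered: 95.0% at 310 per arm and 98.4% at 400.

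**2. Continuous outcome.** Let R² be the share of variance that the covariates explain beyond what the model already uses. The documents do not give it; 0.05 to 0.25 is assumed. Start from 80% power at 400 per arm, so the standardised effect is 1.96 + 0.8416 = 2.8016.

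SE ratio = √(1 − R²); equivalent n per arm = 400/(1 − R²); power = Φ(2.8016/√(1 − R²) − 1.96).

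| R² (assumed) | SE ratio | Equivalent n per arm | Power |
|---|---|---|---|
| 0.05 | 0.975 | 421 | 82.0% |
| 0.10 | 0.949 | 444 | 84.0% |
| 0.20 | 0.894 | 500 | 87.9% |
| 0.25 | 0.866 | 533 | 89.9% |

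**3. Binary outcome.** The formula in step 2 does not apply to logistic regression. Instead, 1,500 trials per setting were simulated with 400 per arm, comparing the unadjusted test with logistic regression on treatment and one prognostic score. The strength of the score is assumed.

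| Odds ratio per SD of score | 20.95% vs 13.5%: raw → adjusted | 20.95% vs 10.475%: raw → adjusted |
|---|---|---|
| 1.35 | 81.1% → 81.6% | 98.8% → 98.7% |
| 1.8 | 80.1% → 82.1% | 98.8% → 99.1% |
| 2.7 | 80.4% → 85.4% | 97.9% → 98.9% |

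The 13.5% rate was chosen only to put unadjusted power near 80%. Simulation error on each power near 80% is about √(0.8·0.2/1500) = 1 point, so the gain in the first row cannot be told from zero.

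**4. What an outcome's own baseline already removes.** With correlation ρ between baseline and follow-up, adjusting for the baseline leaves 1 − ρ² of the variance: 0.96 at ρ = 0.2 and 0.75 at ρ = 0.5 (both assumed). A weakly correlated antenatal diet measure therefore leaves most of the variance for other predictors, and an outcome with no baseline leaves all of it.

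**The case against.** The strongest reply is that the raw tests are not the final analysis. A reader who stops at the sentence on chi-square and t tests might infer that the trial will be judged on them alone. The next sentence rules that out: mixed models are the final analysis of the major outcomes. Where a baseline value exists, as for knowledge, the primary outcome, such a model already uses it. For that outcome baseline knowledge adds nothing new, and only education and income could help.

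Second, a covariate list is commonly left to the full protocol or analysis plan, which is not shown, so its absence alone is no fault. This stands. The point rests instead on what the article does fix: named unadjusted tests as the group comparisons, beside predictors that it names and collects.

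Third, the Interventions section ties these factors to diet and lifestyle, not to disease, and also lists traditional ideas learned from relatives. This too stands. For infection or involution, where the raw test is most exposed, the prognostic value of the covariates is undocumented. For diet it is documented, but a baseline exists.

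Fourth, a reader might infer that a chance imbalance in education or income biases the result. It does not: under randomisation the unadjusted comparison is valid. Nor may the step 2 figures be read across to disease outcomes, because logistic adjustment does not narrow the interval in that way; its gain is in power.

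**Conclusion.** The point holds as a modest, nearly free gain in precision. The stated analyses are valid. Their weakness is that three baseline variables which the protocol itself calls influential are used nowhere, and this counts most for outcomes with no baseline value and for diet.

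The size rests on assumed prognostic strength:

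- continuous outcome at 80% power: about 82% to 90% for an extra R² of 0.05 to 0.25;
- binary outcome near 80% power: about 82% to 85%, a gain of 0.5 to 5 points;
- constipation at the planned effect: almost nothing, as power is about 98% at 400 per arm.

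The binary range needs an odds ratio of 2.7 per SD to reach its upper end, and the documents do not show that education, income or knowledge predict illness that strongly. The documents do not support a claim of bias, or a claim that the trial will be analysed by raw tests alone.

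**What to change.** In Statistical methods, state that the primary between-group estimate comes from a covariate-adjusted model:

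- linear or logistic regression for outcomes measured once;
- the planned generalized linear mixed model for outcomes measured repeatedly.

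Fix three covariates in advance for all of these: education level, family economic situation and baseline knowledge score. For the knowledge outcome, baseline knowledge enters once, as that outcome's own baseline. Keep the chi-square, t and Mann-Whitney tests as unadjusted supporting results. Fixing the covariates beforehand also means that the baseline balance check cannot drive the choice of adjustment.

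The cost is one or two sentences, a little programming and a simple rule for missing covariates. No extra women, visits or questionnaire items are needed. One consequence should be stated in the report: an adjusted logistic model gives a conditional odds ratio, which is not the same quantity as the odds ratio from the raw two-by-two table.

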**Figure 2 F2:**
[figure not shown]
**Social Ecological Model showing potential factors that influence postpartum women's belief and practice**.

Therefore, we have formulated a three-dimension comprehensive intervention strategy (Table 3), which incorporates intervention measures simultaneously to individual postpartum woman, their family members and community environment to maximize the effectiveness of our multicenter trial. For individual postpartum woman, we will set antepartum participatory training courses, provide specially prepared brochures and supporting VCD, set up a specialized counseling hotline and give individual bedside guidance after birth. For their family members, we will invite every postpartum woman's husband and mother to take part in workshops or seminars, making them know some basic knowledge of postpartum care, and persuading them to promote adoption of the diet and lifestyle we advocated by the postpartum woman. For community environment, we will put up posters about basic knowledge of postpartum care in the community bulletin boards for general population educating and mobilize community leaders and heads from and maternal and child health centers for maximum support.

**Table 3 T3:** Summary of our three-dimension comprehensive intervention strategy

Dimensions	Subjects	Strategies and Measures
1	Postpartum woman	- Participatory training for woman who expects to childbirth with 1 month - Providing specially prepared release of "Chinese women's postpartum reasonable diet and lifestyle program" (Universal Edition) and supporting VCD, to facilitate self-learning at home - Setting up a specialized counseling hotline to answer the questions from postpartum woman and their family members - Individual bedside guidance for postpartum woman, focusing on how to correctly adjust her diet and life style during postpartum period

2	Family members	Inviting every postpartum woman's husband and mother to take part in workshops or seminars, making them know some basic knowledge of postpartum care, and persuading them to promote adoption of the diet and lifestyle we advocated by the postpartum woman

3	Community support	- General population educating via putting up posters about basic knowledge of postpartum care in the community bulletin boards - Mobilizing community leaders and heads from and maternal and child health centers for maximum support

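### Part of the intervention is taught in groups in one arm only, and the stated analysis names no allowance for correlation between women taught together

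*Protocol article*

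**What the plan says.** Under Randomization, the protocol article allocates each woman individually by computer-generated random number, and records a unique code and her allocation.

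Under Interventions (the text introducing Table 3), the intervention for the women themselves begins with group teaching: "we will set antepartum participatory training courses". Husbands and mothers are invited to workshops or seminars. The same arm also receives individual components: a brochure and VCD, a telephone hotline and bedside guidance after birth. No group teaching is described for controls. Session size, number of sessions and number of trainers are not given.

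Under Outcome measurements, the primary outcome is change in knowledge and belief about postpartum practice.

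Under Statistical methods, the between-arm tests come first: "Comparisons between intervention group and control group will be performed by Chi-square (categorical variables), t test", with Mann-Whitney for skewed variables. Generalized linear mixed models are then named as the final analyses, with this description: "These models allow for repeated measures and can be used for normally distributed, binomial, and ordinal data". Their random effects are not listed.

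**The concern.** Grouping that arises after randomisation, in one arm only, gives a partially nested design. Women in the same course share a trainer, a delivery of the material and a discussion, so their responses to the intervention may resemble one another. Individual randomisation does not remove that resemblance, and a centre effect common to both arms would not capture it. The knowledge outcome is the most exposed because it is what a course teaches directly.

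A test that assumes independent women then understates the variance of the intervention-arm mean. A mixed model with only a within-woman term does the same, because it deals with repeated measurements on one woman and not with resemblance between women. The treatment interval is too narrow and the nominal 5% level may not hold.

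Timing matters too. A session term can be added to the model later, but only if someone recorded which session each woman attended. The article mentions no such record.

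**Working it through.** **The plan's own figure.** Inputs from the Sample size section: Z for α "is 1.96 when significance level (α) is 0.05"; Z for β "is 1.64 for power (1 - β) is 0.90" (1.64 is used here as printed; its pairing with 0.90 power is a separate matter); control rate p1 = 0.2095; target p2 = 0.10475. Hence the mean rate p̄ = 0.157125 and the difference d = 0.10475.

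n = [1.96·√(2p̄(1−p̄)) + 1.64·√(p1(1−p1) + p2(1−p2))]² / d²

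= [1.96·√0.26487 + 1.64·√0.25939]² / 0.0109726 = 309.89

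This matches the article's 309.89, rounded to 310 per group. The formula treats all women as independent and contains no design effect.

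**Effect of ignoring sessions.** Session size m and ICC are assumptions, since the article gives neither. With equal arm sizes, equal variances and sessions in one arm only:

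- design effect in the intervention arm: DE = 1 + (m − 1)·ICC
- true standard error divided by the one assuming independence: R = √((1 + DE)/2)
- true two-sided error of a nominal 5% test: 2·(1 − Φ(1.96/R))

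| m | ICC | DE | R | True error |
|---|---|---|---|---|
| any | 0 | 1.00 | 1.000 | 5.0% |
| 5 | 0.01 | 1.04 | 1.010 | 5.2% |
| 5 | 0.05 | 1.20 | 1.049 | 6.2% |
| 10 | 0.01 | 1.09 | 1.022 | 5.5% |
| 10 | 0.05 | 1.45 | 1.107 | 7.7% |
| 20 | 0.01 | 1.19 | 1.046 | 6.1% |
| 20 | 0.05 | 1.95 | 1.214 | 10.7% |

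Example, last row: DE = 1 + 19 × 0.05 = 1.95; R = √(2.95/2) = 1.214; 1.96/1.214 = 1.614; 2·(1 − Φ(1.614)) = 0.107.

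**Power once sessions are allowed for** (constipation, n per arm):

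power = Φ((d − 1.96·SE0)/SE1), where SE0 = √(p̄(1−p̄)(1 + DE)/n) and SE1 = √((p1(1−p1) + p2(1−p2)·DE)/n)

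- n = 400: 98% at ICC 0; 96% at m = 10, ICC 0.05; 93% at m = 20, ICC 0.05.
- n = 310, in case attrition takes the arms down to the calculated size: 95% at ICC 0. At m = 20, ICC 0.05, SE0 = 0.0355 and SE1 = 0.0335, so power = Φ((0.10475 − 0.0696)/0.0335) = Φ(1.05) = 85%.

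With the article's own Z values, the calculated size rises from 310 per arm to 371 (m = 10, ICC 0.05) or 439 (m = 20, ICC 0.05). The last exceeds the planned 400.

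**The case against.** A reader might infer that every planned analysis treats women as independent, so that standard errors are necessarily too small and the error rate does exceed 5%. The article does not support this, for four reasons.

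First, the final analysis is a mixed model whose random effects are not listed. Saying that such models allow for repeated measures does not rule out a session or trainer term, and an article may leave that detail to the full protocol or analysis plan. This stands. It does not cover the simple tests, which do assume independence and are named for the comparison between arms, and it does not supply the missing identifier.

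Second, the inflation needs sessions of more than one woman and a positive ICC. Neither figure is given, and bedside guidance, the hotline and the brochure may dilute any session effect. This stands, and it is why the result is a range that starts at 5.0%.

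Third, if the intervention changed nothing for any woman, shared teaching could not create correlation, and individual randomisation would protect the 5% level. The inflation applies when session effects vary but average zero. This stands as a limit on the error-rate claim. It does not rescue the interval: where the effect is real and differs between sessions, an interval that ignores sessions is still too narrow.

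Fourth, family workshop groups need not match the women's course groups, so one session term may not capture both. This also stands, and the fix allows for it.

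**Conclusion.** The point holds as a conditional weakness that is cheap to repair. Part of the intervention is group-taught in one arm, the named between-arm tests assume independence, and the only dependence mentioned for the mixed model is repeated measurement. Followed as written, the plan makes no allowance for session correlation.

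For assumed sessions of 5 to 20 women and an ICC of 0.01 to 0.05 in the intervention arm, a nominal 5% test has a true error of about 5.2% to 10.7%, and the standard error is understated by a factor of 1.01 to 1.21. The lower end is trivial and the upper end is not; the article's figures cannot say where the trial lies. The range also rests on equal arms, equal variances, a large-sample approximation and session effects that vary about a mean of zero. An actual error rate above 5% has not been shown.

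**What to change.** 1. Record the training-session (or trainer) identifier prospectively for each intervention woman.
2. In the final mixed model, add a random effect for session or trainer in the intervention arm only, with control women as singletons, alongside the within-woman term.
3. Take the treatment test and interval from that model, and label the chi-square, t and Mann-Whitney comparisons as descriptive.
4. If family workshop groups differ from course groups, record those as well and examine them in a sensitivity analysis.

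Cost: at least one more recorded variable, one more model term and slightly wider intervals. For constipation at 400 per arm, power stays at 93% or more across the assumed range. If attrition left 310 per arm, it would be 85% in the least favourable case. The article gives no inputs for the same check on the knowledge outcome.
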